#### Multi-method integration

Table 3 displays the RE-AIM [27] dimensions and concepts, source materials, instrument or measurement, and the PRISM [26] dimensions and concepts. As needed, the research team will refer to coded transcript data and quantitative findings to further contextualise results. Using the collective evidence will explore the facilitators and barriers at intervention and control sites. We will rate the influence on each RE-AIM [27] outcome as “positive”, “negative”, or “mixed” (i.e. both positive and negative evidence); we will then compare these across intervention and control. These data will inform progress to and potentially the development of the definitive trial.

**Table 3 Tab3:** PRISM/RE-AIM dimensions and concepts

**RE-AIM dimension and concepts**	**Source material**	**Instrument or measurement**	**PRISM dimension and concepts**
**Reach**			
Inclusion/exclusion criteria	Screening log, HCP interviews; metrics	% screened; % approached; % declined (reasons)	Recipient characteristics and perspectives: Was MMIEAD deemed relevant, accessible, and culturally acceptable by the patients who participated? (intervention only) External environment: Did the external environment (recruitment efforts, advertisement through poster, PIS) facilitate engagement in the trial?
Individuals who enrolled in MMIEAD (intervention sites only)	Collected by the research team	% enrolled. % dropped out	
Characteristics of patients enrolled in trial	Demographic profile, medical records, and CCI	Age, sex, race/ethnicity, marital status, complexity (e.g., comorbidities)	
Patient recruitment	Screening log	Steps utilised by clinical teams to recruit/reach patients	
**Effectiveness**			
Overall feasibility	Adherence data – exercise diaries, 3-day food diaries, tablet count (intervention sites only) Weekly log (from phone calls) Outcome measures Record of AEs and SAEs Patient interviews	% of patients who completed exercise diaries and 3-day food diaries. Nutritics for diet analysis, assess adherence to dietetic advice % of patients who consumed recommended intake of omega-3 fatty fish oil. Identify reasons why adherence potentially affected % outcome measures completed % of related AEs/SAEs Burden of outcome measures	Intervention characteristics: Was MMIEAD adaptable to each individual patient and does it indicate that it is beneficial without causing any harm? (intervention only) Recipient experience: Did patients’ perceptions indicate that the MMIEAD intervention could improve QoL? (intervention only)
Variations in feasibility	HCP interviews	Identify barriers, facilitators, potential reasons for variations in feasibility.	
Patients’ satisfaction with the intervention (intervention sites only)	Patient interviews	Questions on acceptability of trial organisation, physical activity dietary advice, nutritional supplement weekly support.	

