#### Blinding

Due to the nature of the intervention, neither patients nor HCPs can be blinded.

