### Data collection

To ensure consistency across the four study sites, all outcome assessors have undertaken standardised training before data collection begins, with refresher training provided as required. Harmonised data collection protocols, standard operating procedures, and uniform measurement tools will be used across all locations. Regular cross-site monitoring and fidelity checks will be conducted to ensure adherence to procedures and to minimise measurement error.

#### Phase 1

All eligible patients in both intervention arms and control arm will be required to complete baseline and follow up data at 6 weeks and 12 weeks. Longer-term survival (at 6 months and 12 months from the date of recruitment) will also be recorded. Adverse events (AEs) and serious adverse events (SAEs) will be reported using a standard procedure and relatedness will be determined by the clinical team as per our ethically approved reporting structure.

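### The one AE/SAE measure named in Table 3 counts only events judged related by unblinded staff, so it makes no use of the control arm and can miss an excess of non-fatal events

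*Protocol article*

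**What the plan says.** The Overall feasibility row of Table 3 (Effectiveness) gives one measure for adverse events: the percentage "of related AEs/SAEs". It states no denominator. The harm question in the PRISM column of that row reads "does it indicate that it is beneficial without causing any harm? (intervention only" and so concerns the intervention arm alone.

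Under Data collection, Phase 1, AEs and SAEs "will be reported using a standard procedure and relatedness will be determined by the clinical team as per our ethically approved reporting structure". The Blinding section says "Due to the nature of the intervention, neither patients nor HCPs can be blinded".

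Event recording itself is not limited to one arm. The source column of the same row lists "Outcome measures Record of AEs and SAEs Patient interviews" with no arm restriction. The tag for intervention sites in that cell belongs to a different item, "Adherence data – exercise diaries, 3-day food diaries, tablet count (intervention sites only"). The Phase 1 paragraph that holds the AE sentence opens with both arms (times in weeks): "All eligible patients in both intervention arms and control arm will be required to complete baseline and follow up data at 6 weeks and 12".

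The Quantitative analysis (phase 1) section names no AE summary. Survival at 6 and 12 months is recorded from medical notes (Mortality section).

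**The concern.** A related-only measure replaces a comparison with an attribution. The Control arm section says that control patients are not offered MMIEAD, so a control event can hardly be related to it, and the measure has nothing to set beside the intervention arm. In the intervention arm, staff who know the allocation decide which events count. The Strengths and limitations section expects these patients to face many physiological problems as their condition worsens, which makes it hard to attribute a single fall, bleed or admission.

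The Multi-method integration section says that the Table 3 evidence will inform progress to the definitive trial. If the question of harm is answered from this measure alone, an excess over control that clinicians put down to background illness would go unseen, although the events needed to show it appear to be collected in both arms.

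**Working it through.** The article states no event rate, harm threshold or power, so there is no safety figure to reproduce. The sample size can be checked: 4 sites x 10 patients = 40, and 2 sites x 10 = 20 per arm, as stated. The event risks and the intracluster correlation below are assumptions.

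**1. What a related-only count shows when there is an excess.** Let p_c and p_t be the all-cause risks of at least one SAE over 12 weeks in the control and intervention arms. Let f be the share of the excess that clinicians judge related.

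- Expected patients: 20 x p_c in control, 20 x p_t in intervention.
- Expected related count in the intervention arm: 20 x (p_t - p_c) x f.

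| Assumed risks | Control | Intervention | Related, f = 0 | f = 0.25 | f = 0.5 | f = 1 |
|---|---|---|---|---|---|---|
| 20% vs 40% | 4 | 8 | 0 | 1 | 2 | 4 |
| 30% vs 50% | 6 | 10 | 0 | 1 | 2 | 4 |

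The same true excess of 4 patients gives a related count of 0 to 4, and f alone decides which. The all-cause counts (4 vs 8, or 6 vs 10) do not depend on f.

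**2. The missing denominator.** If the percentage is taken over all recorded events, it can fall as harm rises. With 2 related events out of 10 it is 2/10 = 20%. Add 10 further events judged unrelated and it becomes 2/20 = 10%.

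**3. What an all-cause table could and could not show with 20 per arm.**

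- Exact (Clopper-Pearson) 95% intervals: 4/20 = 20% (5.7% to 43.7%); 8/20 = 40% (19.1% to 63.9%). They overlap widely.
- Approximate power of a two-sided 5% comparison, ignoring clustering: 0.28 for 20% vs 40%, and 0.25 for 30% vs 50%.
- With an assumed intracluster correlation of 0.05 and 10 per site, the design effect is 1 + 9 x 0.05 = 1.45 and the effective size is 20/1.45 = 13.8 per arm. Power falls to about 0.20 and 0.18.

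The table would therefore make an excess visible but could not test it.

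**4. Two figures that do not bear on the choice of measure.**

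- Zero events in 20 patients has an exact 95% upper limit of 1 - 0.025^(1/20) = 16.8%. This follows from n = 20 and applies to any zero count, related or all-cause.
- At the 20% one-year mortality in the Background section and a constant hazard, 20 x (1 - 0.8^(12/52)) = 1.0 death per arm is expected in 12 weeks. The eligibility criteria exclude expected survival under 6 months, so this is probably too high, and deaths are captured through survival whatever their attribution.

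**The case against.** The strongest reply is that Table 3 maps measures to an implementation framework and is not a safety analysis plan. Detailed AE tabulation is commonly left to the full protocol or SAP, neither of which is shown, and the article points to a separate, approved reporting structure. That stands as far as it goes: the lack of an AE analysis section is not the point here. The point is that the article names a specific measure, and that measure is a poor one.

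A reader might also infer three stronger claims, which the article does not support.

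- *That harm is judged only through related events.* Survival at 6 and 12 months needs no relatedness judgement. The Quantitative analysis (phase 3) section plans group differences in resource use, and the process evaluation looks at unintended consequences. These are partial substitutes: survival covers only death and has no time point at 12 weeks, and the resource-use measure serves the economic work.
- *That events are collected in the intervention arm only.* The restriction is on the PRISM question, not on the AE record.
- *That the control arm cannot serve as comparator.* It can, because nothing limits event recording to one arm. The Multi-method integration section also plans to compare RE-AIM ratings across arms, but those ratings are positive, negative or mixed and do not commit the plan to an all-cause event table.

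The percentage could also mean the share of all recorded events judged related, which would require the all-cause count. Even so, it would not be a comparison between arms, and step 2 of the working shows that it can move the wrong way.

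Finally, the plan draws no inference about statistical significance, so it does not promise a firm conclusion of no harm. That is a reason to keep the added table descriptive, not a reason to leave it out.

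**Conclusion.** The point holds in a limited form. The only AE/SAE measure that the article names depends on attribution by unblinded clinicians, gives no contrast with control, and sits beside a harm question put to one arm. It can hide an excess of non-fatal events: under the assumed risks, an excess of 4 patients in 20 could appear as anything from 0 to 4 related events. That range illustrates the mechanism and does not predict what this trial will see.

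The conclusion rests on two readings: that related means related to MMIEAD, and that the AE sentence under Data collection covers both arms, as its paragraph suggests. If the full protocol or SAP already tabulates all events by arm, Table 3 only needs to be brought into line.

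**What to change.** In the Overall feasibility row of Table 3:

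1. Beside the related-event measure, add all AEs and SAEs regardless of relatedness, by arm over the 12 weeks, as patients with at least one event and number of events. For the patient proportions give exact 95% intervals, with a note that these ignore clustering by unit. Make no significance test.
2. Keep relatedness as a secondary column and state its denominator.
3. Reword the PRISM harm question so that it asks whether there is a signal of harm relative to control, and remove the intervention-only tag from that part.
4. Flag events found only through the weekly telephone calls. Only the intervention arm receives these calls (Weekly contact section), so they may raise ascertainment there and make MMIEAD look worse than it is.

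Separate lines for falls and bleeding, a breakdown by site, and an identical event prompt in both arms at 6 and 12 weeks would help but are optional.

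The cost is table wording and one extra tabulation of events that the plan appears to record already. The limits are the unequal contact between arms and the small sample, which allows description only.

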**Adoption**			
Level of staff adoption (intervention sites only)	HCP interview	Staff adoption of the MMIEAD intervention - awareness, and receptivity.	Organisational characteristics and infrastructure: Did clinical team deem it a feasible intervention? Were there adequate resources, staff training, and support? External environment: Did specified time allocation for CRN, dietetic, physio encourage uptake, or is more needed?
Patient drop out	HCP interview	% patients dropped out of the trial across intervention and control, reasons.	
Patient participation in MMIEAD (intervention sites only)	Patient interviews	Completers and non-completers issues/challenges, encountered with MMIEAD or personal health.	
**Implementation**			
Adherence to intervention guidelines (intervention sites only)	HCP and patient interviews; metrics from exercise diaries, food diaries, and tablet count	% of patients who completed exercise programme, dietary advice and complied with recommendations for omega-3 supplementation	Implementation infrastructure: Was there adequate feedback, and support for the clinical team from the research team to maintain fidelity? Adaptation support: Did MMIEAD allow for tailoring without undermining core elements?
Adaptations made	HCP interviews	Identify adaptations made, reasons why.	
Feasibility of economic measure	MODRUM, EQ-5D-5L	Feasibility of using these measures for health and social care service use and deriving utility values for the calculation of quality adjusted life years	

*AEs* adverse events, *CCI* Charlson comorbidity index, *CRN* clinical research nurse, *HCPs* healthcare professionals, *MODRUM* Modular resource Use Measure, *MMIEAD* Multi-Modal Integrated intervention combining Exercise, Anti-inflammatory, & Dietary advice, *PIS* participant information sheet, *QoL* quality of life, *SAEs* serious adverse events

#### Missing data

As this is a feasibility study, the primary aim regarding missing data is to assess its extent, patterns, and potential sources to inform procedures for a future definitive trial. Missing quantitative data will not be imputed; instead, descriptive analyses and exploratory sensitivity checks will be conducted to understand the impact of missingness. For qualitative data, interviews or focus groups that are incomplete or not recorded due to participant withdrawal will not be replaced, and analysis will proceed using available transcripts. All missing data will be documented and reported transparently.

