#### Processes

##### Recruitment (phase 1 and 3)

Our recruitment rate is anticipated to be two patients per month per site. The sample size for the feasibility study is 40 patients, collectively 20 per intervention arm, 20 per control arm, based on providing sufficient information to inform the primary outcomes [40]. The study is being supported by Northern Ireland Clinical Research Network (NICRN).

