### Analyses

#### Quantitative analysis (phase 1)

Quantitative data will be coded and entered into the Statistical Package for the Social Sciences (IBM SPSS Statistics Version 24). Data on participant eligibility, recruitment, refusal, and retention will be assessed as proportions and rates. Demographic characteristics and adherence to the intervention components will be reported with descriptive statistics as appropriate, for instance, reporting of mean standard deviation (SD) for interval scale variables and frequency/percentages for categorical variables. Differences between control and intervention groups at baseline will be assessed using chi-squared tests and independent *t*-tests. Potential effective outcomes will estimate the effect size and be analysed for mean change using pair sample *t*-tests to compare the difference pre and post intervention, and repeated measure analysis of variance (ANOVA) to consider interactions. However, given that this is a feasibility study, no inferences will be made regarding statistical significance, given that the sample size is not powered to make such assertions. Data from the 3-day food diary will be entered into Nutritics for diet analysis to estimate dietary protein and energy intake. By using Nutritics software (www.nutritics.com - version 3.1), this will enable analysis of compliance with food-based dietary guidelines [63].

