In quantitative analyses, there is little consensus on the appropriate sample size for a feasibility study, with guidance ranging from 12 per arm [70] to 50 per arm [71]. The justification for larger sample sizes in feasibility studies is often based around obtaining narrow standard deviations on outcome measures to maximise precision in a future power calculation [71]. However, there is disagreement over whether this is an appropriate method to inform power calculations as this would in turn increase the likelihood of identifying a statistically significant effect during the feasibility stage, which can be inappropriately reported, call into question the validity of the effect, and reduce the likelihood of a follow-up RCT [72–74]. As per the CONSORT extension [75], feasibility studies should focus on the acceptability of trial processes or an intervention, including recruitment, the time needed to collect and analyse data, and response rates to outcome measures. The overall evaluation of MMIEAD will require a multi-methods approach, with both quantitative and qualitative data. In qualitative analyses, for the process evaluation, simulations have shown that a sample size of 10 should identify 80% of problems within a complex intervention [76] while data saturation is likely to be reached at 12 interviews on average [41]. The principle of 10 plus five for data saturation outlines that a minimum of 10 interviews should be conducted, followed by potentially 5 consecutive interviews that present no new findings [77]. A formal sample size calculation is not appropriate for feasibility studies as the objectives do not include establishing the effectiveness of an intervention.

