### Strengths and limitations

The multi-phase study design, guided by the RE-AIM-PRISM framework [26, 27], will generate evidence of feasibility and implementation outcomes to build a strong definitive RCT and further refine our ToC model [20]. However, complex interventions contain several interacting components and present practical and methodological difficulties, such as standardising its design across two study sites, and adapting it to ensure it does not negatively impact on standard care [79]. Through our PRISM/RE-AIM design of MMIEAD, we have been circumspect in preparing for potential contextual implementation challenges [26]. The potential barriers and/or logistical challenges are described as follows, together with the mitigation strategies for overcoming them.We are aware that standard care may differ at site level; therefore, we plan to record these differences through the process evaluation.The on-site research team is small consisting of three staff with placement agreements for each site; one member of the research team will be responsible for intervention delivery, and therefore to enhance validity, this researcher will not be involved in interviewing participants from the intervention sites for the process evaluation.To ensure consistency in measurements, all on-site research team members have collectively conducted training in physical assessments (BIA, HGS, EFS, SPPB, MUAMC, TSF).We understand that the HCPs involved may experience staffing difficulties and unprecedented pressure; therefore, we have designed the trial to minimise unnecessary burden and support has been ongoing and delivered during online and in-person study set-up meetings.To ensure all member of our wider expert reference group stay informed about study progress, we have scheduled regular meetings and monthly newsletters with reminders and information related to the intervention, to ensure all members are kept updated.Patients receiving haemodialysis with or at risk of kidney cachexia are likely to be subject to multiple physiological challenges as their condition deteriorates which may affect adherence to MMIEAD. In planning this study, we have worked closely with consultant nephrologists who are our local collaborators to ensure that data collection points will coincide with planned dialysis, and routine clinical data already available (such as monthly blood tests performed in all dialysis patients as part of their standard care) will be used to minimise any potential additional burden to patients. Furthermore, PPIE representatives have provided expert patient knowledge and experience from inception taking account of any potential patient burden.

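### The phase 1 repeated-measures ANOVA with no imputation bases the arm-by-time estimate on patients seen at all three visits and discards the other patients' observed data

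*Protocol article*

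**What the plan says.** Under Data collection, phase 1, patients in both arms are "required to complete baseline and follow up data at 6 weeks and 12 weeks", which makes three assessments. The planned sample is given under Recruitment (phase 1 and 3): "The sample size for the feasibility study is 40 patients, collectively 20 per intervention arm, 20 per control arm".

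Quantitative analysis (phase 1) names two methods for the clinical outcomes. The first is a paired t-test of pre to post change: "Potential effective outcomes will estimate the effect size and be analysed for mean change using pair sample" t-tests. The second is a "repeated measure analysis of variance (ANOVA) to consider interactions". Effect sizes are to be estimated, and inference about statistical significance is disclaimed. The software is SPSS version 24, with no procedure named.

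The Missing data section states: "Missing quantitative data will not be imputed; instead, descriptive analyses and exploratory sensitivity checks will be conducted to understand the impact of missingness". It also makes the extent, patterns and sources of missingness an aim in themselves and promises transparent reporting.

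**The concern.** Each element is reasonable alone, but they combine badly. Classical repeated-measures ANOVA needs a complete row per patient. With three visits and no imputation, a patient seen at baseline and week 6 but not at week 12 contributes nothing to the interaction, although two of the three values were observed. A patient who misses only week 6 is also lost.

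The interaction matters because it is the only phase 1 analysis that compares change between the arms. The paired t-tests work within a group, and the chi-squared and independent t-tests are confined to baseline. With 20 patients per arm, discarding observed data costs precision. If the patients lost differ from those kept, the estimated effect size describes a selected group.

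**Working it through.** **Inputs from the article.** Four sites of 10 patients: 4 × 10 = 40, and 2 × 10 = 20 per arm, which agrees with the stated sample. Three visits, no imputation. There is no power calculation to reproduce: "A formal sample size calculation is not appropriate for feasibility studies as the objectives do not include establishing the effectiveness of an intervention".

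**Input assumed.** The article gives no expected rate of missed visits or dropout. Take a proportion m missing at each follow-up visit, from 5% to 20%, with baseline complete.

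**Patients kept, visits missed independently.** Repeated-measures ANOVA keeps 40 × (1 − m)². A baseline-to-week-12 paired t-test keeps 40 × (1 − m).

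| m per follow-up visit | ANOVA, three visits | Paired t-test, two visits |
|---|---|---|
| 5% | 40 × 0.95² = 36.1 | 38.0 |
| 10% | 40 × 0.90² = 32.4 | 36.0 |
| 15% | 40 × 0.85² = 28.9 | 34.0 |
| 20% | 40 × 0.80² = 25.6 | 32.0 |

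**Patients kept, monotone dropout.** If everyone missing at week 6 is also missing at week 12, and m is the total lost by week 12, both analyses keep 40 × (1 − m): 38.0 at 5% and 32.0 at 20%. The ANOVA then loses no more patients than the t-test. It still ignores any week-6 values of those who leave later.

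**Does the loss bias the change?** Illustration: SD 1 at each visit, all correlations 0.7, true baseline-to-week-12 change −0.30 SD, and 20% lost at week 12. Let the worst 20% on some variable leave, the sharpest form of selection. The completers' mean on that variable then rises by 0.280/0.80 = 0.35 of its SD (0.280 is the normal density at the 20th percentile). The effect on the completers' mean change depends on which variable it is:

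- Loss at random: no shift, change −0.30.
- Loss by poor week-6 level: the covariance of change with the week-6 value is 0.7 − 0.7 = 0, so change stays at −0.30.
- Loss by decline from baseline to week 6: the decline has variance 2 − 1.4 = 0.6 (SD 0.775) and covariance with change of 0.7 − 0.7 − 0.7 + 1 = 0.3, so the slope is 0.3/0.6 = 0.5. Change = −0.30 + 0.5 × 0.35 × 0.775 = −0.16.
- Loss by poor baseline: the slope is 0.7 − 1 = −0.3. Change = −0.30 − 0.3 × 0.35 = −0.405.

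Softer selection falls between these values and −0.30; simulation agreed. Completers can therefore understate the decline, show it correctly or overstate it. Levels are a separate matter: with 10% to 30% loss driven by the week-6 level, simulation put the completers' means about 0.06 to 0.18 SD above the truth while the change stayed unbiased.

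**The case against.** The strongest reply is that little in this feasibility trial rests on the ANOVA. Pre to post mean change comes from paired t-tests, which need two visits. The primary outcomes are recruitment and retention. Progression depends on recruitment, acceptability and component compliance. Significance is disclaimed, and the Discussion reports disagreement over using feasibility SDs for power calculations. All of this stands and limits the point to the interaction. It does not remove the point: effect sizes are to be estimated, and disclaiming significance does not restore discarded data or correct a selected estimate.

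A second reply is that the Missing data section already plans sensitivity checks and descriptive work. It does, but the article does not say what the checks contain, and the main interaction estimate stays complete-case.

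A third is that the article never mentions listwise deletion, and that the choice of procedure belongs in an analysis plan that is not shown. The article does, however, name both the method and the no-imputation rule, and deletion follows from the two together.

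A reader might infer that all outcome estimates describe only patients well enough to attend three times, or that a fixed share of the decline would be hidden. The documents support neither reading. Patients are described as "likely to be subject to multiple physiological challenges as their condition deteriorates which may affect adherence to MMIEAD", which concerns adherence rather than attendance, and the same section says that data collection coincides with planned dialysis. The 20% one-year mortality in the Background, at a constant hazard, gives 1 − 0.8^(12/52) = 5.0% by week 12, or about 2 of 40. Even that is only illustrative, because patients with expected survival under 6 months are excluded. Selection by health is plausible but not established.

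**Conclusion.** The point holds for the arm-by-time interaction. As specified, that analysis uses only patients with all three visits and discards observed values from the rest. It keeps about 36 to 26 of 40 if 5% to 20% miss each follow-up visit independently, and the same number as the baseline-to-week-12 paired t-test if dropout is monotone. These rates are assumptions, and so is the reading of the ANOVA as the classical three-visit procedure with arm by time as the interaction of interest. Bias in the estimated change is possible, but its size and sign cannot be fixed from the documents. The point is not fatal to a feasibility trial, but it is worth correcting because the remedy is cheap.

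**What to change.** Replace the repeated-measures ANOVA with a likelihood-based linear mixed model for repeated measures, fitted with SPSS MIXED to all observed visits, with terms for visit and arm-by-visit. Keep baseline in the outcome vector. If baseline enters only as a covariate, a patient with no follow-up visit contributes nothing. The no-imputation policy stands, because the model uses observed values only.

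Name the three-visit completer analysis as one of the sensitivity checks already promised, and report the number analysed by arm and visit for each outcome.

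The cost is a few sentences, slightly more modelling work in the same software, and no added burden on patients. The model relies on data being missing at random given the observed values. That assumption should be stated, and the comparison with the completer analysis shows how far the result depends on which patients are included.
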